## Study design and randomization

The VR-USP study follows a Prospective Randomized Open, Blinded Endpoint (PROBE) three-arm clinical trial design with a 1:1:1 allocation ratio. The trial protocol was reviewed and approved by the Institutional Review Board (Protocol Number: CAAE 74,181,523.0.0000.0068) and prospectively registered in a primary clinical trial registry (Registry Number: NCT07063394). To evaluate the intervention’s robustness within a diverse cardiothoracic population, a block randomization sequence, consisting of twenty fixed blocks of three, is generated by an independent statistician utilizing Microsoft Excel software. This pragmatic approach is selected to reflect real-world clinical heterogeneity, ensuring that the trial’s findings maintain high external validity for routine intensive care workflows. Allocation concealment is ensured through the use of sequentially numbered, opaque, and tamper-evident sealed envelopes, numbered from 1 to 60. These envelopes are stored in a locked cabinet controlled by an independent clinical nurse who has no contact with the trial participants. Furthermore, the specific envelope for each participant is only released to the research team after a designated investigator obtains the appropriate consent documents, including parental consent and minor assent for patients under 18 years of age, and enrolls the patient. Consequently, the recruiters remain blinded to the allocation sequence prior to inclusion, and the assigned intervention arm is revealed only post-enrollment, thereby maintaining appropriate allocation concealment.

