## Standard of care framework

Irrespective of group allocation, all participants receive the institutional standard multimodal anesthesia and analgesia protocol, which is managed by the Acute Pain Service. Intraoperatively, all patients undergo a standardized general anesthesia regimen, including continuous hemodynamic monitoring (5-lead electrocardiogram, pulse oximetry, non-invasive and invasive arterial blood pressure) and controlled mechanical ventilation. Crucially, to provide preventive analgesia and mitigate the neuroendocrine stress response associated with major surgical trauma, early analgesic interventions—incorporating regional techniques such as thoracic epidural placement (T5-T12) or fascial plane blocks, tailored to the specific surgical approach—are systematically performed immediately following anesthetic induction and prior to the surgical incision. Postoperatively, this regimen employs a balanced strategy integrating peripheral analgesics, nonsteroidal anti-inflammatory drugs, and targeted opioid administration. In the immediate postoperative phase, pain is controlled through intravenous morphine titration, consisting of 2 mg boluses administered every 5 to 10 min until a Visual Analogue Scale score below 3 is achieved.

Subsequently, analgesic maintenance is provided via Patient-Controlled Analgesia pumps. These devices utilize a standardized 0.5 mg/ml morphine solution, programmed for demand boluses of 0.5 to 1.0 mg with a 7 to 15 min lockout interval. Furthermore, pain intensity is systematically evaluated as a vital sign during routine hemodynamic checks utilizing the Visual Analogue Scale (VAS). Concurrently, the Richmond Agitation-Sedation Scale (RASS) is monitored by the ICU clinical team as a safety and eligibility parameter. To ensure protocol fidelity and patient safety, a Virtual Reality session is only initiated if the patient is in an optimal state of alertness, defined as a RASS score between −1 (drowsy) and +1 (restless). Patients presenting with severe agitation (RASS ≥ +2) or deep sedation (RASS ≤ −2) will have their sessions postponed until clinical stabilization. Consequently, the uniform application of this baseline framework across all study arms ensures that any variations in cumulative opioid consumption can be attributed directly to the digital interventions being investigated.

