## Trial procedures and data collection

The protocol begins in the preoperative phase with a systematic cognitive screening applied to all potential participants. Specifically, the Mini-Mental State Examination (MMSE) is administered to every patient prior to surgery, including those subsequently randomized to the control group, to ensure a baseline of cognitive function that is homogeneous across the entire cohort. Furthermore, once clinically stabilized after surgery and extubated in the ICU, randomized patients start their assigned VR sessions from the first to the fifth postoperative day. The target duration for each session is 45 min to maximize the immersive analgesic effect. However, to prioritize patient comfort and mitigate visual fatigue, the protocol permits a voluntary early cessation at 30 min based on spontaneous patient requests, thereby defining the 30 to 45 min therapeutic window. These sessions are performed three times daily. The total cumulative time of hardware exposure is recorded for each participant to ensure a standardized evaluation of the immersive therapeutic dose across all intervention groups. Specifically, this therapeutic dose will be analyzed as a continuous variable, calculated by summing the total minutes across all 15 sessions. Early interruptions are not classified as protocol deviations, but rather as expected natural fluctuations in patient tolerance, being appropriately captured as a lower cumulative dose within the Intention-to-Treat (ITT) framework.

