Data collection begins upon enrollment, encompassing demographic variables, biometric indices, and baseline clinical risk stratification. Specifically, the American Society of Anesthesiologists physical status classification will be assessed for the entire cohort, while the EuroSCORE II will be calculated for patients undergoing cardiac procedures. Preoperative cognitive function is quantified using the Mini Mental State Examination. Additionally, intraoperative parameters, including cardiopulmonary bypass duration, total anesthesia time, and intraoperative opioid titration, are recorded to account for potential confounding variables in the postoperative analgesic response. To ensure maximum data integrity and adherence to good clinical practice guidelines, all gathered clinical information will be securely entered and managed using the Research Electronic Data Capture (REDCap) electronic data capture tools hosted at the institution.

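### The envelope may be opened at enrolment, apparently before surgery, although the arms do not differ until the first session after extubation; releasing it at that point would close an avoidable route to bias in opioid use

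*Protocol article*

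**What the plan says.** **Release of the envelope** (Study design and randomization). An independent nurse holds the envelopes: "the specific envelope for each participant is only released to the research team after a designated investigator obtains the appropriate consent documents" and enrols the patient. The section adds that "the assigned intervention arm is revealed only post-enrollment". Surgery, extubation and the first session are not mentioned as conditions.

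**Timing of enrolment** (Sample size and study population; Trial procedures and data collection). A preoperative Mini-Mental State Examination (MMSE) score is a mandatory inclusion criterion. The test "is administered to every patient prior to surgery, including those subsequently randomized to the control group". "Data collection begins upon enrollment, encompassing demographic variables, biometric indices, and baseline clinical risk stratification"; the same paragraph goes on to intraoperative parameters.

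**First difference between arms** (Trial procedures and data collection). "once clinically stabilized after surgery and extubated in the ICU, randomized patients start their assigned VR sessions from the first to the fifth postoperative day".

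**Care in between** (Standard of care framework). All arms receive the same institutional regimen, "incorporating regional techniques such as thoracic epidural placement (T5-T12) or fascial plane blocks, tailored to the specific surgical approach", performed after induction and before incision. Intravenous morphine is then titrated in the immediate postoperative phase. Bypass duration, anaesthesia time and "intraoperative opioid titration, are recorded to account for potential confounding variables in the postoperative analgesic response".

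**Blinding and model** (Table 1; Statistical analysis plan). Only the pain assessors and the statistician are blinded. The operating-room anaesthesia team and the Acute Pain Service have no row. The primary model names surgical type as its covariate.

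**The concern.** Allocation concealment before enrolment is well covered. The gap is the interval between enrolment and the first session. If the envelope is opened at enrolment, the arm is known through anaesthesia and early recovery, when it has no operational use but care that affects opioid need is being given.

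The primary endpoint is MME consumed postoperatively. An arm-related shift in block type, intraoperative opioid or early morphine would move that endpoint and be read as an effect of VR. Objective pump logs prevent mismeasurement; they do not prevent a real difference in care. The standard-of-care section attributes differences in opioid consumption directly to the digital interventions, which requires care before the first session to be independent of arm.

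The status of the intraoperative variables is a second issue. They are recorded as possible confounders, but under the stated release rule they can fall after allocation. Adjusting for a variable that allocation can influence may itself introduce bias.

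**Working it through.** The protocol states no figure on this point, so the check is first one of sequence.

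**Sequence**

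| Step | What the protocol fixes | Arm may be known? |
|---|---|---|
| MMSE screening | Before surgery, before randomization | No |
| Consent and enrolment | Before surgery by implication; data collection starts here | No |
| Envelope release | Any time after consent and enrolment | Yes, from here |
| Regional block, intraoperative opioid | Same regimen in all arms; technique fitted to surgical approach, opioid titrated | Yes |
| Immediate postoperative morphine titration | Same regimen in all arms; counts as postoperative MME | Yes |
| Extubation, readiness, first session | Arms first differ | Yes, and now needed |

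The sentence that starts sessions after extubation already calls the patients randomized, which fits opening before that point. Nothing postpones opening to it.

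**Illustration of size**

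From the protocol: 20 patients per arm and a 0.05 significance level. Assumed: a two-sided test; an effect of intraoperative technique on MME of 0.5 to 1.0 SD; and a difference in its use between two arms, caused by knowledge of the arm, of 0 to 30 percentage points. The protocol gives neither of the last two.

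- Bias in SD = effect of technique × difference in use.
- Noncentrality = bias × √(20/2) = bias × 3.162.
- Rejection probability with no VR effect: two-sided noncentral t with 60 − 3 = 57 df.

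| Effect (SD) | Difference in use | Bias (SD) | Noncentrality | False-positive rate, one contrast |
|---|---|---|---|---|
| any | 0 | 0 | 0 | 5.0% |
| 0.5 | 0.10 | 0.05 | 0.158 | 5.3% |
| 0.8 | 0.20 | 0.16 | 0.506 | 7.9% |
| 0.8 | 0.30 | 0.24 | 0.759 | 11.6% |
| 1.0 | 0.30 | 0.30 | 0.949 | 15.4% |

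A normal approximation gives 5.3% and 15.8% for the smallest and largest non-zero bias. The calculation ignores adjustment for surgical type, which would absorb any part of the difference in technique that follows the surgical approach.

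**The case against.** **Opening before surgery is inferred.** Consent and enrolment set an earliest bound for release, not a clock time. The intraoperative variables are listed without an order and could be extracted later from the health record. The exclusion for ventilation at the time of the scheduled intervention can be checked only after surgery. This stands: preoperative opening is the natural reading and is permitted, but it is not fixed.

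**No disclosure to anaesthetists is described.** The envelope goes to the research team. Care is given irrespective of allocation, the block is tied to surgical approach, and surgical type is in the primary model. Bias therefore needs the arm to reach the clinicians, a departure from the common regimen, and a shift within surgical type. This also stands. A reader might infer that intraoperative care will differ by arm, or that the anaesthetists will know the arm; the documents support neither. They leave the route open: the patient is unblinded and can mention the arm, Table 1 gives those teams no status, and titrated opioid leaves room for judgement.

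**No stated model adjusts for intraoperative variables.** Correct. They are only said to be recorded, so harm from adjustment would arise only if they were used.

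**The unblinded period to day 5 is the larger exposure.** Probably so, and the protocol declares it. But that exposure cannot be avoided once sessions begin; this one can.

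**Later release would place some opioid use before randomization and dilute the contrast.** This does not hold. Opioid given before the first session counts towards postoperative MME under either timing. Later release only makes that part independent of arm.

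**Conclusion.** The point holds as a cheap improvement to a stated rule, not as a demonstrated error. The rule permits the arm to be known from enrolment, which the text implies is preoperative, although the arms do not separate until after extubation. That is an avoidable route to bias in the primary endpoint.

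Its size is unknown. The false-positive rate of a single contrast is 5.0% if the common regimen is followed equally in all arms, and about 15% at the extreme of the assumed inputs (1.0 SD and 30 points). These figures illustrate scale and do not estimate what will happen. The conclusion rests on preoperative enrolment being the intended reading. If the full protocol already delays opening until after extubation, the article needs only to say so.

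**What to change.** 1. In Study design and randomization, keep consent, MMSE and enrolment before surgery. State that the nurse releases the next envelope only after surgery, once the patient is extubated and meets the protocol's existing conditions for a first session. Record that check and its time for every patient, future controls included, before the envelope is opened.
2. State that intraoperative opioid, block type, anaesthesia time and bypass time then precede randomization and may safely be used as covariates.
3. State whether the MME window starts at the end of surgery or at randomization. With late release, opioid given before randomization is independent of arm in either case.

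**Gain beyond bias.** The modified intention-to-treat set keeps only randomized patients who received the allocated intervention and had at least one later assessment. Randomizing at readiness leaves fewer patients to be lost between allocation and first session.

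**Cost.** A sentence or two of text and an instruction to the nurse; the envelopes, sample size and clinical care are unchanged. Any arm-specific VR training would take place after surgery, and envelopes must be retrievable from postoperative day 1.

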## Standard of care framework

Irrespective of group allocation, all participants receive the institutional standard multimodal anesthesia and analgesia protocol, which is managed by the Acute Pain Service. Intraoperatively, all patients undergo a standardized general anesthesia regimen, including continuous hemodynamic monitoring (5-lead electrocardiogram, pulse oximetry, non-invasive and invasive arterial blood pressure) and controlled mechanical ventilation. Crucially, to provide preventive analgesia and mitigate the neuroendocrine stress response associated with major surgical trauma, early analgesic interventions—incorporating regional techniques such as thoracic epidural placement (T5-T12) or fascial plane blocks, tailored to the specific surgical approach—are systematically performed immediately following anesthetic induction and prior to the surgical incision. Postoperatively, this regimen employs a balanced strategy integrating peripheral analgesics, nonsteroidal anti-inflammatory drugs, and targeted opioid administration. In the immediate postoperative phase, pain is controlled through intravenous morphine titration, consisting of 2 mg boluses administered every 5 to 10 min until a Visual Analogue Scale score below 3 is achieved.

Subsequently, analgesic maintenance is provided via Patient-Controlled Analgesia pumps. These devices utilize a standardized 0.5 mg/ml morphine solution, programmed for demand boluses of 0.5 to 1.0 mg with a 7 to 15 min lockout interval. Furthermore, pain intensity is systematically evaluated as a vital sign during routine hemodynamic checks utilizing the Visual Analogue Scale (VAS). Concurrently, the Richmond Agitation-Sedation Scale (RASS) is monitored by the ICU clinical team as a safety and eligibility parameter. To ensure protocol fidelity and patient safety, a Virtual Reality session is only initiated if the patient is in an optimal state of alertness, defined as a RASS score between −1 (drowsy) and +1 (restless). Patients presenting with severe agitation (RASS ≥ +2) or deep sedation (RASS ≤ −2) will have their sessions postponed until clinical stabilization. Consequently, the uniform application of this baseline framework across all study arms ensures that any variations in cumulative opioid consumption can be attributed directly to the digital interventions being investigated.

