## Virtual reality interventions

For the intervention arms, a progressive additive model is applied to ensure clear methodological differentiation. Group 3 serves as the control and receives the institutional standard multimodal anesthesia and analgesia protocol. To maintain high external validity and reflect real-world intensive care conditions, pharmacological management and rescue analgesia for all groups are strictly governed by the institutional Standard Operating Procedure for Acute Pain Management. According to this protocol, pain is objectively assessed during every routine vital sign check. Adequate pain control is institutionally defined as a Visual Analogue Scale (VAS) score of 3 or less. Consequently, subjective bedside dosing is minimized, as any reported pain score of VAS ≥ 4 (categorized as moderate to severe pain) triggers mandatory re-evaluation and the administration of standardized rescue interventions—including oral, intermittent intravenous, or PCA titrations—until the target of VAS < 3 is achieved. Furthermore, to preserve the pragmatic nature of the trial, participants in the control group are not restricted from using standard non-immersive personal devices, such as smartphones or hospital televisions. Restricting access to these devices is considered ethically and logistically inviable due to the essential need for family communication during a critical postoperative period and the inherent setup of shared hospital rooms. Therefore, this study is pragmatically designed to evaluate the supplementary efficacy of virtual reality immersion against the baseline noise and unstructured digital distractions that already constitute the real-world standard of care. This methodological allowance is further grounded in the premise that the therapeutic mechanism of virtual reality relies on multisensory immersion, which fundamentally differs from the limited cognitive engagement provided by conventional two-dimensional screens.

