## Clinical endpoints and blinding

The primary clinical endpoint is defined as the cumulative morphine milligram equivalents consumed postoperatively, which is objectively quantified throughout the entire evaluation period. This fundamental outcome is monitored by tracking patient-controlled analgesia pump dosing logs to accurately record both requested and administered boluses. By assessing total opioid consumption within a pragmatic clinical framework, the study captures the intervention’s efficacy as an adjunct to routine postoperative analgesic management, accounting for the inherent clinical variability of an intensive care setting. Furthermore, due to the randomized design, it is assumed that exposure to institutional sedation protocols, chest physiotherapy, and intensive care environmental noise will be homogeneously distributed across all three arms, thereby neutralizing the influence of these confounding factors when comparing the intervention and control groups. To ensure accurate comparative analysis, all administered opioids, including rescue doses of medications such as tramadol, will be converted into cumulative morphine milligram equivalents according to standardized international pharmacological guidelines. Concurrently, the total daily consumption of non-opioid rescue analgesics, specifically dipyrone and paracetamol, will be independently calculated and recorded as the total cumulative daily dose in milligrams.

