In parallel, as a crucial secondary clinical outcome, pain intensity is measured using the Visual Analogue Scale (VAS) at rest and during movement, which is specifically elicited by instructing the patient to take a deep breath. Evaluating dynamic pain represents the clinical gold standard, as joint practice guidelines from the American Pain Society and the American Society of Anesthesiologists emphasize that assessing pain during movement or activity is essential to accurately capture postoperative discomfort and guide functional recovery [21]. These VAS assessments are conducted at predefined and standardized time points throughout the day, ensuring temporal consistency across all three study arms. To clarify the Prospective Randomized Open, Blinded Endpoint (PROBE) design, we have explicitly defined the blinding status of all involved personnel. Due to the physical and highly visible nature of the Virtual Reality headsets, complete double-blinding is structurally impossible. Therefore, to mitigate detection and performance bias, a strict blinding matrix is established (Table 1).

**Table 1 tbl0001:** Blinding matrix for the PROBE design.

Role	Blinding Status	Justification / Mitigation Strategy
Participants	Unblinded	Inherent to the use of highly visible VR equipment.
VR Application Team	Unblinded	Researchers responsible for device setup and safety monitoring.
ICU Clinical Team	Unblinded	Cannot be blinded due to the shared, open ICU environment.
Pain Outcome Assessors	Blinded	Distinct staff exclusively assessing VAS. Patients are instructed daily not to discuss VR.
Statistician	Blinded	Data delivered with masked group codes (e.g., Group A, B, C).

By completely separating the personnel who administer the VR sessions from the clinical professionals who assess the Visual Analogue Scale (VAS) scores, the outcome assessors remain blinded to the assigned intervention. Additionally, the primary endpoint (cumulative opioid consumption) is quantified objectively via automated PCA pump logs and standardized medical records, structurally preventing expectancy bias from the outcome assessors.

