## Limitations

A primary limitation of this protocol is the inability to perform a double-blind study due to the nature of the intervention, as both the participants and the research team are inherently aware of the use of Virtual Reality (VR) headsets. Consequently, this lack of blinding may introduce a performance bias in the subjective reporting of pain levels through the Visual Analogue Scale (VAS) and in the evaluation of patient satisfaction via the PSQ 18 questionnaire. Additionally, patients allocated to the standard care control group might experience resentful demoralization. Knowing they are excluded from the novel technological intervention could negatively influence their subjective psychological state and artificially lower their satisfaction scores.

In addition, a notable limitation inherent to this study design is the presence of attention and expectancy biases. Patients allocated to the VR intervention arms inherently receive more direct, continuous attention from the research team during the setup and supervision of the sessions compared to the standard care control group. This discrepancy in social interaction, combined with the novelty effect of using an immersive technological device, may generate a positive expectancy or placebo effect that independently contributes to pain reduction and anxiety relief. While the use of an objective primary endpoint—cumulative opioid consumption, rigorously calculated by tracking both automated PCA pump logs and electronic medical records (encompassing oral and intermittent intravenous doses)—helps mitigate the subjectivity of self-reported pain scores (VAS), the psychological impact of receiving specialized, dedicated attention cannot be entirely isolated from the specific analgesic effects of the VR therapy itself.

In addition, environmental factors in the Intensive Care Unit, such as excessive noise, frequent clinical interruptions, or the presence of multiple invasive lines and chest tubes, may also severely limit the degree of immersion achieved by the patient.

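### The primary opioid endpoint is objectively recorded but not blinded, so a difference between arms belongs to the assigned package and cannot be attributed directly to VR

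*Protocol article*

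**What the plan says.** Standard of care framework closes by saying that applying the same analgesic protocol to all arms "ensures that any variations in cumulative opioid consumption can be attributed directly to the digital interventions being investigated". The same section gives the patient-controlled analgesia (PCA) settings as ranges, "programmed for demand boluses of 0.5 to 1.0 mg with a 7 to 15 min lockout interval", and places analgesia under the Acute Pain Service.

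Study design and randomization describes a PROBE design, that is, open treatment with blinded endpoint assessment. The specifications table calls the trial open-label.

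Clinical endpoints and blinding: "The primary clinical endpoint is defined as the cumulative morphine milligram equivalents consumed postoperatively". Table 1 in that section lists participants as unblinded ("Inherent to the use of highly visible VR equipment") and the ICU clinical team as unblinded ("Cannot be blinded due to the shared, open ICU environment"). The blinded roles are the VAS assessors and the statistician. The text below the table says that pump logs and records make the primary endpoint objective, "structurally preventing expectancy bias from the outcome assessors".

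Virtual reality interventions says that "subjective bedside dosing is minimized", because a reported VAS of 4 or more triggers standardized rescue by oral, intravenous or PCA routes.

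Limitations says that the effect of dedicated attention "cannot be entirely isolated from the specific analgesic effects of the VR therapy itself".

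**The concern.** A pump log is an exact record of doses, but those doses follow from decisions. The patient who presses the button knows the arm. Rescue follows a score which that patient reports, in a unit whose staff know the arm. Blinding a separate VAS assessor protects a secondary outcome and leaves open the behaviour that produces the primary one.

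Two statements then fail. The attribution sentence claims more than the design can deliver and conflicts with the Limitations section. The PROBE label invites the reader to treat MME as the blinded endpoint.

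The stake is interpretation. Expectancy in the VR arms, disappointment in controls and arm-aware rescue could each produce a difference in MME that would be read as an analgesic effect of VR. The trial is meant to supply efficacy signals and variance estimates for definitive trials, so such a bias would carry forward.

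**Working it through.** **1. Who generates the endpoint, and who is blinded**

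- *PCA demands:* made by the participant, unblinded (Table 1).
- *Rescue trigger:* VAS of 4 or more, reported by the same participant (Virtual reality interventions). It is scored at routine vital-sign checks. The protocol does not say whether the blinded VAS assessors take those triggering scores.
- *Rescue delivery:* oral, intermittent intravenous or PCA titration, in a unit whose clinical team is unblinded (Table 1).
- *Pump programming:* analgesia is managed by the Acute Pain Service, which Table 1 does not list. Whether those who set the pump know the arm is not stated.
- *Recording of the dose:* automated logs and medical records. This step is objective.
- *Blinded roles:* VAS assessors and statistician. Neither generates MME.

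The accurate description is therefore: objectively recorded, openly generated.

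**2. Attribution claim against Limitations**

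The first section assigns any variation directly to VR. Limitations says that attention effects cannot be fully separated from it. Both cannot stand. Limitations also names performance bias only for VAS and the PSQ-18, and offers opioid use as the mitigation, so its disclosure does not reach the primary endpoint.

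Clinical endpoints and blinding argues that randomization balances sedation protocols, physiotherapy and noise. That argument covers background exposures. It does not cover behaviour that differs by arm after allocation.

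The extra attention is substantial. A professional stays at the bedside throughout each session (Safety protocols), so supervised time in the VR arms is up to 3 × 45 min = 2.25 h a day, and 5 × 2.25 = 11.25 h in total, which matches the protocol's own maximum. Controls have no sessions.

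**3. Latitude in the pump range**

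The protocol states no maximum hourly dose, so there is no figure to reproduce. Maximum deliverable dose = bolus × 60 / lockout:

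- Low extreme: 0.5 × 60/15 = 2.0 mg/h.
- High extreme: 1.0 × 60/7 = 8.57 mg/h.
- Ratio: 8.57/2.0 = 4.29 (4.0 to 4.5 if only whole boluses per hour are counted).

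This is a ratio of ceilings. It is not a ratio of opioid actually used, and it does not measure bias.

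**4. What a bias would do at this sample size (illustration)**

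Inputs: 20 per arm (Sample size and study population); significance level 0.05 (Statistical analysis plan), taken as two-sided because sidedness is not stated. The bias *b*, in SD units, is an assumption, since the protocol gives neither an SD for MME nor a bias size. With no true VR effect, SE = SD × √(2/20) = 0.316 SD, and

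P(significant) = 1 − Φ(1.96 − b/0.316) + Φ(−1.96 − b/0.316).

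| Assumed bias (SD) | P(significant pairwise difference) |
|---|---|
| 0 | 5.0% |
| 0.1 | 6.2% |
| 0.2 | 9.7% |
| 0.3 | 15.8% |
| 0.5 | 35.3% |
| 0.8 | 71.6% |

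This is a simple two-mean z-test and not the planned mixed model. It shows only the order of magnitude.

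**The case against.** The best defence is that much of this is declared. The specifications table says open-label, Table 1 lists patients and ICU staff as unblinded, and Limitations discusses attention, novelty, expectancy and placebo effects. Results are framed as preliminary signals, and the rescue trigger gives some structure to dosing. This stands as far as it goes. It does not rescue the attribution sentence, and the disclosure stops short of opioid use.

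Four stronger readings are tempting, and the documents do not support them.

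- *Unblinded staff set the pump across a fourfold range.* The Acute Pain Service manages analgesia and its blinding is not stated. The fourfold span concerns maximum deliverable dose only.
- *The claim about preventing expectancy bias is false.* It is limited to outcome assessors, and for recording of the dose it is fair. The error would be to extend it to dosing.
- *The VAS trigger and blinded assessors protect nothing.* If blinded assessors take the triggering scores, there is some protection. The protocol leaves this open.
- *The headset itself suppresses button presses.* Session time is at most 2.25/24 = 9.4% of a day, or 2.25/16 = 14.1% of an assumed 16 waking hours. To lower MME by that share, every session must run the full 45 minutes, demand must be even over time, and every press must be lost and never made up. Hands are occupied mainly in the gaming arm, someone is at the bedside throughout, and fewer requests during distraction is also the hypothesised mechanism. These figures are upper bounds on a what-if.

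**Conclusion.** The point holds as a mismatch between claim and design. Randomization supports attributing a difference in MME, beyond chance, to the assigned package: VR, staff attention and analgesic behaviour by people who know the arm. It does not support attributing it directly to VR, and MME is not a blinded endpoint in the sense that the PROBE label suggests.

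This rests on current text: Table 1, the endpoint definition, and the conflict between Standard of care framework and Limitations. The size of any bias is unknown. The 9.7% and 35.3% figures depend on assumed biases of 0.2 and 0.5 SD. A reader should not infer that bias is shown to exist or that its size can be read from the pump range. Open treatment is unavoidable here; the overclaim is not. The correction is worth making before results are reported, because it changes what the trial may conclude.

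**What to change.** 1. **Standard of care framework:** replace the attribution sentence with one that assigns any difference to the package as allocated (VR, staff attention and open-label analgesic behaviour).
2. **Study design and randomization; Clinical endpoints and blinding:** state that blinded assessment applies to VAS and that MME is an objectively recorded open-label endpoint. Keep the sentence on outcome assessors, limited to recording of the dose. A line in Table 1 giving the status of the Acute Pain Service would settle what is now unstated.
3. **Limitations:** say that performance and expectancy bias can also reach opioid use.
4. **Supportive analysis:** keep total MME as the single primary endpoint, so that no multiplicity is added. Report separately by arm the patient-demanded PCA MME, with requested against delivered boluses, and the staff-administered MME. Tabulate the pump settings used by arm.

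The protocol already collects requested and administered boluses from the pump logs, and other opioid doses from medical records. Pump settings are assumed to be retrievable from the same sources. No dose or clinical rule changes.

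The cost is a less favourable design label and a few extra tables. The split will not by itself separate VR from attention or expectancy. It shows whether a difference lies in what patients asked for or in what staff gave.

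Excluding session time from the analysis is not advised: controls have no sessions, so their windows would have to be invented, and the exclusion removes the time when distraction should act. Fixing the pump setting before the envelope is opened is not workable as the plan stands, because envelope release is not tied to the start of the pump.
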